# Peer group-based online intervention program to empower families raising children with disabilities: protocol for a feasibility study using non-randomized waitlist-controlled trial

**DOI:** 10.1186/s40814-022-01190-1

**Published:** 2022-11-02

**Keywords:** Disabled children, Family, Family empowerment, Caregiver burden, Health care service, QOL, Peer group, Online program, Non-randomized waitlist-controlled trial

## Abstract

**Background:**

Families raising children with disabilities assume risks to their health and lives. Therefore, it is necessary to support these families to improve family empowerment, which is the ability of these families to control their own lives and to promote the collaborative raising of children with disabilities. This is the first online intervention program focusing on the empowerment of families raising children with disabilities who live at home in Japan.

**Method:**

The program consists of four online peer-based group sessions. Moreover, the families engage in several activities in stages wherein they discover their own issues, find measures to resolve them, and take action, while visualizing interfamily relationships, including social resources, and the status of their family life, with facilitators and other peer members. This study is a non-randomized, waitlist-controlled trial. It compares the results of the intervention group (early group) and the waitlist-controlled group (delayed group). The participants are allocated to the early or delayed group in the order of their applications. The main outcome is family empowerment. Other outcomes are the caregiver burden, self-reported capability to use social resources, self-compassion, and the quality of life (QOL) of primary caregivers. The timeline of the online outcome evaluation is as follows: the initial evaluation (Time 1 [T1]) is conducted before the start of the first early group program, and post-intervention evaluation (Time 2 [T2]) is conducted immediately (within 1 week) after the early group completes all four sessions (4 weeks) of the program. Follow-up evaluation (Time 3 [T3]) is conducted 4 weeks after the post-intervention evaluation. This timing is the same in the delayed group, but the delayed group will attend the program after a 4-week waiting period, compared to the early group.

**Discussion:**

The intention is to evaluate whether the provision of the program developed in this study and the evaluation test design are feasible and to verify the efficacy of this program.

**Trial registration:**

The UMIN Clinical Trials Registry (UMIN000044172), registration date: May 19, 2021.

**Supplementary Information:**

The online version contains supplementary material available at 10.1186/s40814-022-01190-1.

## Background

With highly advanced medical treatment enabling lifesaving techniques and shortened hospital stays, there are an increasing number of children with severe disabilities who are cared for at home, from childhood. In Japan, there has been a rapid increase in the number of children with severe disabilities who need constant medical care. According to the Ministry of Health, Labor and Welfare, the number of children with severe disabilities aged 0–19 years who need constant medical care was 9403 in 2005, and this number has doubled to 20,155 in 2020 [1].

Families raising children with disabilities face much higher risks to their own health and lives, compared to families raising healthy children. The mother, who is usually the primary caregiver, carries the burden of time and responsibility associated with providing the required care to the child and thus tends to have poor mental health [2]. Thus, there is an urgent need for direct support for families raising children with disabilities.

The concept of empowerment began to be used in the field of health sociology since the 1980s in the USA and from the 1990s in the UK [3, 4]. Family empowerment is the ability of families to control their own lives and to promote the collaborative raising of children with disabilities [5]. Collaborative partners who might be involved in raising children include other family members, medical and social service professionals, school teachers, and government officials. Koren et al. proposed a conceptual framework of empowerment for families raising children with disabilities in the community. This framework consists of “empowerment of family (internal) relationships,” “empowerment of relationships with service systems,” and “empowerment of interactions with the community” [6]. In Japan, the concept of empowerment was introduced in 1999 in the Guidelines for Support Services, including Care for People with Disabilities [7], and the concept of “family as a whole” for children with disabilities and their families was presented.

The mental health of mothers raising children with disabilities is related to their empowerment. Previous research has shown that depressive symptoms are associated with lower empowerment among mothers raising children with disabilities [8]. Also, mothers raising children with developmental disabilities participated in health-promoting activities infrequently; moreover, depressive symptoms, maternal empowerment, and two indicators of child-related QoL explained significant variance in healthy behaviors [9]. Parents often face a variety of difficulties in raising children with disabilities. Therefore, these parents need to be able to not only receive social resources including healthcare services but also use and coordinate social resources that are necessary for their children and families. In addition, these parents need the skills to cope with child- and family-related problems.

In a previous study, we conducted in-depth interviews with 34 families with children with severe disabilities who lived at home (mother, father, and siblings aged 12 years and older) [10] and conducted a questionnaire survey of 158 nurses and government officials using the Delphi method [11] to comprehensively list the factors that comprise the family empowerment model. Thereafter, we issued a self-administered questionnaire based on that model to 1659 families nationwide with children with severe disabilities who were living at home, to develop and verify the family empowerment model [12]. This research undertaken with family caregivers has shown an association between the empowerment and knowledge of social resources and how to use these resources in order to reduce burden. However, the above were observational studies. In this study, we verify, through implementational research, whether an intervention for each of these factors (specifically, by working on increasing the “self-reported capability to use social resources” and reducing the “caregiver burden”) can actually increase family empowerment. Furthermore, we aim to determine which of the three levels of Koren et al.’s conceptual framework (“family [internal] FA”, “service system SS,” and “community SP”) are actually empowered by this intervention.

### Purpose

This paper describes the development and implementation of a peer group-based online intervention program to empower families raising children with disabilities. The primary objective of this study is to explore the feasibility of delivering a non-waitlist randomized controlled trial to a group-based intervention program of the “Family Empowerment Program of families raising children with disabilities” in the community. The secondary objective is to determine whether the peer-led, online group-based Family Empowerment Program for families raising children with disabilities is more effective at empowering families and reducing the caregiver burden and improving the self-reported capability to use social resources, self-compassion, and health-related quality of life (HR-QOL) of families raising children with disabilities. We have developed and now plan to evaluate, the first online program designed to empower families caring for children with disabilities who live at home, in Japan.

## Method

### Study design and setting

This study is a non-randomized, waitlist-controlled trial. We compare the group starting the family empowerment program a week after the initial evaluation (intervention/early group) to the group starting delayed intervention (waitlist-controlled/delayed group). This study is registered as a clinical trial in the UMIN Clinical Trials Registry (UMIN000044172). The study protocol has been prepared in accordance with the Standard Protocol Items: Recommendations for Intervention trials (SPIRIT) 2013 statement [13]. The trial and flow of participants through the trial are illustrated in the flow chart (Fig. 1). The SPIRIT schedule of enrollment, interventions, and assessments are presented in Fig. 2. The SPIRIT Checklist can be found in Additional file 1. This protocol is version 1, dated June 2021.

**Fig. 1 Fig1:**
[figure not shown]
Trial flow chart

**Fig. 2 Fig2:**
[figure not shown]
The SPIRIT schedule of enrollment, interventions, and assessments

### Recruitment methods

A written request for cooperation in the study is sent by post to people in charge of medical institutions, government agencies, and special-needs schools nationwide. The organizations that are requested to cooperate are specialized medical institutions and rehabilitation centers for children with physical disabilities, university hospitals and specialist pediatric hospitals, medical welfare departments of local governments, and special-needs schools for children with physical impairment or chronic diseases.

People in charge of organizations who consent to cooperate in the study are requested to display posters to recruit program participants within their facility and distribute flyers explaining the research to people who match the inclusion criteria and do not fall under the exclusion criteria. The flyers describe the general outline of the family empowerment program, the schedule, target participants, and implementation method. People interested in the study are requested to access a dedicated website from the information in the flyer and apply to participate in the study after consenting to the content of the study’s flyer. To reach the target sample size, requests for study cooperation may also be sent to associations for families with disabled children and day care centers for children with disabilities, depending on the status of participant registration.

### Inclusion criteria and exclusion criteria

Target participants are family caregivers who are primarily caring for children under the age of 20 with physical, intellectual, or developmental disorders, at home. Exclusion criteria include people who are unable to read or write in Japanese, and those who are unable to connect to the Internet.

### Sample size

The sample size is estimated by selecting *F* tests (ANCOVA) using G*Power software version 3.1.9.7 [14]. The required sample size is calculated based on data obtained from the pretest implemented with the same subjects and equivalent program content as used in this study. The required sample size is 52, assuming an effect size of 0.33, a test power of 80%, and an *α* value of 0.05. The dropout rate is assumed to be 10% based on a previous study with an online program for parents of children with disabilities [15]. From a feasibility study perspective, a formal sample size calculation is not essential. Our sample size calculation is based on the pragmatics of recruitment and the necessity for examining feasibility among a broad group of families caring for children with disabilities.

### Intervention allocation

Participants are allocated to the early or delayed group in the order of their applications. A maximum of 20 people can participate in each program, and the family empowerment program comprising a total of four group sessions is implemented several times per month. Participants in both groups will not be told the timings of the intervention or the evaluations in the other group in an attempt to keep all participants blinded as to which group they are allocated to. Facilitators of the family empowerment program cannot be blinded to the participants’ allocations because they need to contact the participants and respond to inquiries. The analysts are blinded to the allocation of participants.

### Reducing the risk of participant drop-out

To reduce the risk of participant drop-out, we ensure that participants can contact the principal investigator directly by email or telephone with any questions about participation before enrolling in the program. In addition, after deciding to participate, participants receive individual confirmation emails, with information regarding the arrival of the program textbook and guidance on participation methods, before the program’s start date. Each participant is also sent reminders to respond to questionnaires required for program evaluation, depending on the available response timeframe and response status of each participant.

### Ethical considerations

The protocol for this study was reviewed and approved by the institutional review board established by the principal investigator’s affiliated institution. Voluntary written informed consent is obtained from the participants before the initial evaluation. The explanatory document for this study includes matters that need to be explained to the participants according to the “Ethical Guidelines for Life Science and Medical Research Involving Human Subjects” formulated by the Ministry of Health, Labor and Welfare. That is, it includes information on the purpose and significance of the study, the study methods, the burden on the study subjects, expected risks and benefits to the subjects, management of personal information, methods to store and dispose of information, and financial burden on the study subjects. The study subjects can freely choose to participate or abstain from the study without being disadvantaged in any way. Their declaration of intent to participate in the study may be withdrawn at any time without providing a reason. Moreover, participants’ personal information and data remain confidential. The data collected in this study, including the questionnaire responses, are stored for a certain period, even after the end of the study.

### Intervention methods

The intervention program for this study is developed using an intervention mapping approach [16]. We have developed a peer group-based support program based on the social cognitive theory [17], a taxonomy of behavior change techniques (BCTs), and a practical behavior change technique [18], as an intervention method to encourage changes in family behavior, with the aim of improving family empowerment in families raising children with disabilities who live at home. The described intervention has been further extracted using the “Better reporting of interventions: template for intervention description and replication (TIDieR) checklist and guide [19].” The specific development process for the intervention used in this study is described in a separate paper [20].

The program holds a total of four weekly group sessions every Saturday afternoon continuously for 1 month using an online meeting system (ZOOM®). Each session is scheduled for two hours. In each group session, participants are separated into two to four sub-groups (around three to six people per group) of smaller online rooms (breakout rooms), in line with the type of disability and the age of the child. During this time, participants share their opinions, questions, and answers. In every session, the discussion time of the online smaller rooms is for at least 60 min. At the start and the end of the session, all the participants gather together. At the end of the session, facilitators share their impressions of the session with the whole group. The participants receive a textbook by post approximately 1 week before the first program. Four to six researchers take turns as the program facilitators each time. The main facilitators are fixed for all four sessions, while three to four facilitators are responsible for encouraging sharing among participants in breakout rooms and following up with participants about the online meeting system.

The program details are as follows. In the first session, each participant creates and shares an eco-map [21] with the aim of “understanding the current circumstances surrounding the child and the family,” while reflecting upon their own lives and the lives of their disabled children and their families at the present time. Finding elements of family empowerment in each participant’s life leads to a basic understanding of family empowerment. Furthermore, participants’ sharing of their eco-maps in the group promoted mutual understanding among them and which may have the secondary effect of promoting group dynamics. In the second session, all participants share their homework, which is to create a table to record a week in their lives between the first and second sessions, with the aim of “reflecting on the child’s and the family’s actual life to clarify the participant’s desired life.” Time is set aside for participants to think about problems in their current lives and to imagine the kind of life they want for themselves and their families. In the third session, participants engage in a clear goal-setting exercise to achieve the kind of life they want for themselves and for their families and set specific behavior goals to achieve that end; they share this information with the group. Participants think of goals, such as “I would like to be able to work full time in the 3 years later”, or “I would like to take the whole family on an overnight trip in the next year.” Time is set aside to think in relation to each domain of family empowerment, which links “What can be done within the family? (FA),” “What can be done with service providers (SS),” and “What can be done with government officials in the local community? (SP).” In the fourth session, participants share their “efforts to work toward the life they want,” which is the homework between the third and fourth sessions; they also reflect on the group work as a whole.

Throughout the program described above, participants are reminded to set clear goals based on the characteristics of their families, on raising a child with disabilities, to promote self-monitoring, to provide information, to clarify barriers to benefits and risks related to health and life, to promote peer support, to promote self-compassion, and to promote awareness of family empowerment.

Interactions between parents and children at different developmental stages aim to provide the opportunity for parents with younger children to acquire information on their outlook for the future and for parents with older children to self-monitor by looking back on their progress to date. This program is based on peer groups; therefore, the facilitators devise ways to ensure that the participants’ initiative and interaction among members are demonstrated in the sessions. Specifically, facilitators try to create a relaxed situation by allowing participants to speak more and by allowing other members to freely express their opinions in response to members’ comments. This program is repeated over a period of about 6 months.

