### Personal education tools

We prepared three types of tools: a workbook, a booklet on family empowerment as a sub-textbook, and an online meeting system manual. The textbook, booklet, and online meeting system manual are distributed to the program participants. The online meeting manual, which describes the use of Zoom® is distributed and made available online. The textbook was printed in color, and innovations were added, such as large font and large sheets of paper for homework, to ensure that the participants could comfortably participate in the program. A certificate of completion was inserted at the end of the textbook, and after participating in the last session, a PDF copy of the certificate of completion was emailed to the participants, with the aim of improving self-compassion. The booklet is used as a tool to promote awareness of family empowerment. An explanation of the three levels of family empowerment and explanations of each item were provided with illustrations, ensuring that the participants can easily refer to the content during the program and can link the content to family empowerment and their situations.

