### Data collection method

In order to evaluate the effectiveness of this program, data is collected from participants through an online survey. Participants are invited to complete online questionnaires that assess their family empowerment, caregiver burden, self-reported capability to use social resources, self-compassion, and quality of life. A survey request email is sent to the participants regarding the online survey at the times described below, and one or more reminders are sent to those who do not respond. Participants are requested to cooperate in the survey regardless of their program attendance. For example, even if a participant does not attend any sessions, they are asked to complete the survey.

The online survey is conducted at the following three time points. After the participants apply for the program and are allocated to either the early or delayed group, they are notified of their attendance month (from July to December). At the time, participants are not informed if they are in the early or delayed group; they are simply notified of their attendance month to prevent response bias based on the participant’s impression of their allocated group. Thereafter, the initial evaluation (Time 1 [T1]) is conducted before the early group starts the first session. For the early group, this corresponded roughly to a week before attending the program. The post-intervention evaluation (Time 2 [T2]) is conducted immediately (within 1 week) after the early group completed all four sessions in the program (4 weeks). The follow-up evaluation (Time 3 [T3]) is conducted 4 weeks after the post-intervention evaluation. The timings are the same for the delayed group; however, it begins the program precisely 4 weeks after the early group does. That is, the delayed group completes the evaluation for T1 roughly 5 weeks before attending the program, T2 immediately before attending the program, and T3 immediately after completing the course.

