The response information is collected in the online survey system. Participants are allocated identity documents (IDs) that are linked to the response information, and every response of each participant from T1 to T3 can be linked. If there are multiple responses from the same person at the same time (duplications), it is assumed that it is because the respondent wished to correct their answer; hence, the later response is adopted. The data collected in the online survey system are backed up fortnightly. Once all the participants complete the follow-up evaluations, the data are downloaded from the system and stored as primary raw data.

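### Textbook delivery and the delayed group's T2 fall in the same week, so some control FES values may be recorded after program material has arrived

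*Protocol article*

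**What the plan says.** On materials, Intervention methods states: "The participants receive a textbook by post approximately 1 week before the first program". The sentence covers all participants and does not treat the two groups differently. Personal education tools says that a booklet on family empowerment is also distributed and describes its content: "An explanation of the three levels of family empowerment and explanations of each item were provided with illustrations". It gives no delivery date for the booklet.

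On timing, Data collection method places T2 within one week of the early group's fourth session. Of the delayed group it says that "it begins the program precisely 4 weeks after the early group does", and that it completes "T2 immediately before attending the program, and T3 immediately after completing the course". Of T1 it says: "For the early group, this corresponded roughly to a week before attending the program". The delayed group's T1 is about five weeks before its own start.

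On use, Data analysis makes total FES at T2 the measure of effectiveness. It is compared between groups by ANCOVA with total FES at T1 as covariate. Paired t tests then compare T2 with T3 in the delayed group, to see whether the effect is reproduced, and T1 with T3 in the early group, to see whether it lasts. Feasibility outcomes names feasibility as the primary outcome of the study as a whole.

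**The concern.** A waitlist control value should be measured before the control group meets any part of the intervention. Here the delayed group's T2 serves both as the control value for the between-group comparison and as the starting value for that group's own before-and-after test. The textbook carries the program's exercises, and the booklet explains the three levels that FES scores. If either is in hand when a control answers T2, that answer is no longer strictly unexposed.

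The early group has the matching problem at T1. Its baseline is taken at about the time its textbook is due, while the delayed group's T1 comes about four weeks before its textbook is due. The covariate may therefore be measured under different conditions in the two groups.

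Nothing in the article holds the material back until the relevant survey has been answered.

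**Working it through.** **Inputs**
- Four weekly sessions; textbook about 1 week before the first (Intervention methods).
- Early T1 about 1 week before its first session; T2 within 1 week after its fourth; T3 4 weeks after T2; delayed group starts 4 weeks after the early group (Data collection method).

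**Day count, with T1 = day 0**

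| Event | Calculation | Day |
|---|---|---|
| Early textbook | 7 − 7 | about 0 |
| Early session 1 | 0 + 7 | 7 |
| Early session 4 | 7 + 3 × 7 | 28 |
| T2 window | 28 to 28 + 7 | 28 to 35 |
| Delayed session 1 | 7 + 28 | 35 |
| Delayed textbook | 35 − 7 | about 28 |

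**Check against the plan's own figures.** Delayed session 1 on day 35 is 35 / 7 = 5 weeks after T1, which matches the stated interval of roughly five weeks. T3 falls on days 28 + 28 = 56 to 35 + 28 = 63. Delayed session 4 is on day 35 + 21 = 56, so T3 comes just after that group finishes, as stated. The schedule is read correctly.

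**Overlap.** The delayed textbook is due about day 28 and T2 runs from day 28 to day 35. Possible exposure before T2 is therefore about 0 days for a control who answers as the window opens, and about 7 days for one who answers just before session 1.

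**Direction.** The ANCOVA estimate is

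(early mean T2 − delayed mean T2) − b × (early mean T1 − delayed mean T1),

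where b is the slope on T1, taken as positive. Suppose the material raises mean FES by u in the delayed group at T2 and by v in the early group at T1.
- Between groups: the estimate falls by u + b × v.
- Delayed group, T2 to T3: the mean change falls by u.
- Early group, T1 to T3: the mean change falls by v.

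The documents give no value for u, v or b, so no size can be attached.

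**The case against.** Several stronger readings are tempting, and the documents do not support them.

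**That all controls are exposed before T2.** Both times are approximate and T2 opens at about the time the textbook is due. A prompt responder may answer before the post arrives, and receiving a workbook is not the same as reading it. Only possible exposure, varying between people, can be claimed.

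**That controls certainly hold an explanation of the FES construct.** That description belongs to the booklet, and only the textbook's delivery is dated. The article says the booklet is for reference while the program runs. It may travel with the textbook, but this is not stated. Most of the active work (eco-map, weekly record, goal setting) takes place in sessions or as homework between them.

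**That T2 answers given after delayed session 1 would count.** The duplicate rule says "it is assumed that it is because the respondent wished to correct their answer; hence, the later response is adopted", and a reader might extend this to late answers. It applies only to repeat responses at the same survey point. T2 for this group is placed before the program starts, and the section on reducing drop-out refers to a response timeframe. Closing dates are detail that an article may leave to the full protocol.

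**That a loss of power can be quoted.** Any such figure would need an assumed share of the program effect carried by the printed material, for which the documents offer nothing.

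It is also fair to say that, if the material raises FES, the bias works against the program and would not create a positive result. Recruitment, retention and acceptability are untouched. What survives all of this is that the two stated times coincide, and nothing in the article puts the survey before the material.

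**Conclusion.** The point holds as a scheduling overlap. Followed as written, the plan can place program material with some delayed-group participants up to about 7 days before the FES measurement that serves as their control value. It can likewise place material with early-group participants at about the time of their baseline. The conclusion rests on reading the textbook sentence as applying to both groups, which is its plain sense, and on the approximate times being roughly kept.

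The effect on FES is unknown. Shrinkage of the adjusted T2 difference, and of the delayed group's T2 to T3 change, is conditional on the material raising FES. That is the program's intention, but the article gives no data on it.

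The consequence is confined to the effectiveness analyses; feasibility is unaffected. This is a modest, avoidable bias worth removing because the remedy is cheap. It does not invalidate the study. A later analysis plan could not undo exposure that had already occurred, so the order needs to be set in the conduct of the trial.

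**What to change.** 1. Dispatch the textbook and booklet to each participant only once that person's pre-program survey is logged: T1 in the early group, T2 in the delayed group. State the booklet's delivery date as well as the textbook's.
2. Set a fixed latest dispatch date before session 1, so that non-responders do not start without materials. An individual trigger is needed because the T2 window runs up to session 1. Waiting for the whole survey to close would leave almost no time for the post.
3. Record dispatch dates and survey time stamps. The article already plans confirmation emails about the textbook's arrival, which could help to date receipt.
4. Add a sensitivity analysis of the T2 comparison that excludes delayed-group T2 responses given after the material arrived. Read it as supportive only, since prompt and late responders may differ in other ways.

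The cost is some mailing logistics and a shorter lead time with the textbook for some participants, mainly those who answer late. The sensitivity analysis will also use fewer controls.
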